## **20.6 Subject confidentiality**

The trial staff will ensure that the subjects' anonymity is maintained. The subjects will be identified only by initials and a subject's identification number on the CRF and any database. All documents will be stored securely. The study will comply with the Data Protection Act.

## **21 FINANCING AND INSURANCE/INDEMNITY**

The UNIVERSITY COLLEGE OF DUBLIN is the SPONSOR and will ensure that every investigator is covered by a Public Liability ('negligent harm') insurance that applies for the clinical trial. All investigators are qualified and practicing physicians and are thus insured by the clinical indemnity scheme (CIS).

The study will be funded by Chiesi Farmaceutici (Parma, Italy).

## 22 CLINICAL STUDY REPORT AND PUBLICATION POLICY

The clinical study report will be drafted in compliance with the regulatory requirements and Sponsor's standard operating procedure.

The sponsor's representative and the Chief Investigator must mutually agree on the final version. One copy of the final report will be dated and signed by the Chief Investigator and the Legal Representative of the Sponsor.

The responsibility for publication of the data obtained from this study lies with the study Chief Investigator. Neither the sponsor, nor any of the study funders, will have any involvement in data collection, data review, data analysis or preparation of the publication manuscript or in the decision to submit for publication.

### Revision history

| Revision | Justification   | Timing   |
|----------|-----------------|----------|
| 1.0      | Initial Version | 27/04/22 |
|          |                 |          |
|          |                 |          |

# 1. Introduction

## 1.1 Background and rationale

Many preterm infants develop respiratory distress syndrome (RDS), a condition characterised by a relative lack of surfactant. Endotracheal surfactant therapy revolutionised the care of preterm infants in the 1990s. However, supporting newborns with RDS with continuous positive airway pressure (CPAP) and reserving endotracheal surfactant for those who develop respiratory failure despite CPAP yield better results than intubating all infants for surfactant. Half of preterm infants born before 29 weeks gestation initially managed with CPAP are intubated for surfactant. Intubation is difficult to learn and associated with adverse effects. Surfactant administration into the oropharynx has been reported in preterm animals and humans and may be effective. We wished to determine whether giving oropharyngeal surfactant at birth reduces the rate of endotracheal intubation for respiratory failure in preterm infants within 120 hours of birth.

## 1.2 Objectives

The primary objective is to investigate the efficacy of prophylactic oropharyngeal surfactant for reducing the rate of endotracheal intubation, compared to no intervention in infants at risk of RDS.

The secondary objective is to investigate the efficacy of prophylactic oropharyngeal surfactant compared to no intervention for preventing some possible complications in premature infants at risk of RDS. We will also record a number of variables relating to prematurity, from enrolment into the trial until discharge home from hospital.

## 1.3 Endpoints

### Primary endpoint

The primary endpoint is the incidence of endotracheal intubation for respiratory failure within 120 hours of birth.

Enrolled infants will be intubated for persistent apnoea and/or bradycardia in the DR, or for respiratory failure in the NICU defined as  $\geq 2$  of:

- Clinical signs – worsening tachypnoea; grunting; subcostal, intercostal and/or sternal recession
- Acidosis – pH < 7.2 on 2 blood gases (arterial or capillary)  $\geq 30$  minutes apart
- $O_2$ -FiO2 > 0.4 to keep SpO2  $\geq 90\%$  for > 30minutes
- PCO2 > 9.0 kPa on 2 blood gases (arterial or capillary)  $\geq 30$  minutes apart
- Apnoea – recurrent apnoea treated with mask ventilation

The frequency of blood gas monitoring is based on the clinical decision of the treating physician, as per routine practice.

|         |                                           |              |              |
|---------|-------------------------------------------|--------------|--------------|
| UCD CRC | SAP for the POPART trial                  |              |              |
| UCD CRC | Template: Statistical Analysis Plan (SAP) | Version: 1.0 |              |
|         |                                           |              | Page 5 of 19 |

Enrolled infants will only be intubated if they reach the pre-determined criteria for respiratory failure. Attending clinicians may give endotracheal surfactant via a thin catheter (LISA technique) or via an endotracheal tube (ETT). After giving endotracheal surfactant for the treatment of RDS, attending clinicians may attempt to extubate the babies immediately ("INSURE") or they may elect to ventilate the babies for a longer period. This is at their discretion.

#### Secondary endpoints:

- Intubation in the delivery room (**dr\_infant\_intub.factor**)
- Number of attempts taken to successfully intubate in the DR ( **dr\_infant\_intubation\_attempts** )
- Chest compressions in the DR ( **chest\_compressions.factor** )
- Adrenaline administration in the DR (**adrenaline.factor**)
- Rectal temperature on admission to the NICU ( **nicu\_rectal\_temp** )
- NICU intubation – first intubation occurring in the NICU ( **first\_intubation\_nicu.factor** )
- Surfactant use before death or hospital discharge
  - Number of doses, including total dose
  - Intra-tracheal surfactant received post-intervention ( **ett\_postrandom.factor** )
  - Doses of post-intervention surfactant ( **ett\_postrandom\_dose\_no** )
- Respiratory distress syndrome ( **resp\_distress\_syndrome.factor** )
  - Clinical evidence of respiratory distress with radiological evidence (ground glass appearance on CXR)
- Incidence of pneumothorax (**pneumothorax.factor**)
  - Incidence of pneumothorax on CXR
- Incidence of pulmonary haemorrhage (**pulm\_haem.factor**)
  - Clinical evidence of pulmonary haemorrhage
- Mechanical ventilation ( **mechanical\_ventilation.factor** )
- Days of mechanical ventilation ( **mech\_vent\_days** )
- Use of postnatal corticosteroids for ventilator dependence ( **post\_steroids.factor** )
- Days of duration of respiratory support (endotracheal ventilation, high-frequency oscillatory ventilation, CPAP, heated humidified high-flow nasal cannula O2, low flow nasal cannula O2) (**resp\_supp\_days**)
- Bronchopulmonary dysplasia (BPD) –supplemental O2 at 28 days of life ( **o2\_d28.factor** )
- Chronic lung disease of prematurity (CLD) – need for supplemental O2 at 36 weeks corrected gestational age (CGA) determined by physiological oxygen reduction test ( **o2\_36wks.factor** )
- Medical treatment for a patent ductus arteriosus ( **pda\_medtr.factor** )
  - Administration of ibuprofen or paracetamol for PDA
- Surgical treatment for a patent ductus arteriosus ( **pda\_surgery.factor** )
- Proven necrotising enterocolitis (≥ Bell's stage 2) ( **proven\_nec.factor** )
- Incidence of Intraventricular haemorrhage (IVH) (any (**ivh\_any.factor**) and severe (**ivh\_severe.factor**): IVH grade ≥ 3)
  - Evidence on surveillance cranial ultrasounds performed regularly in NICU as standard of care

|         |                          |  |
|---------|--------------------------|--|
| UCD CRC | SAP for the POPART trial |  |
|---------|--------------------------|--|

|         |                                           |              |              |
|---------|-------------------------------------------|--------------|--------------|
| UCD CRC | Template: Statistical Analysis Plan (SAP) | Version: 1.0 |              |
|         |                                           |              | Page 6 of 19 |

- Incidence of cystic periventricular leukomalacia (**cystic\_pvl.factor**)
  - Evidence on surveillance cranial ultrasounds performed regularly in NICU as standard of care
- Retinopathy of prematurity treated with laser photocoagulation or intravitreal injections (**retinopathy\_tr\_req.factor**)
  - Evidence on surveillance ophthalmology review performed regularly in NICU as standard of care
- Death before hospital discharge ( **hospitalisation\_death.factor** )
- Survival without BPD at hospital discharge ( **without\_bpd\_at\_discharge.factor** )
- Survival without CLD at hospital discharge ( **without\_cld\_at\_discharge.factor** )
- Duration of hospitalisation ( **hospitalisation\_duration** )
- Use of home oxygen therapy (**home\_oxygen.factor**)
  - Discharged home on oxygen therapy

These are clearly defined outcome measures and will be recorded during the infants hospital stay prior to discharge home from hospital. These outcome measures include complications of prematurity that can occur at any stage from birth until discharge home and thus specific timeframes for measurement is not applicable in all cases.

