### Secondary outcomes

- Intubation in the delivery room (DR)
- Number of attempts taken to successfully intubate in the DR
- Chest compressions in the DR
- Adrenaline administration in the DR
- Rectal temperature on admission to the NICU
- NICU intubation
- Surfactant use before death or hospital discharge
  - Number of doses, including total dose
  - Intra-tracheal surfactant received post-intervention
  - Doses of post-intervention surfactant
- Respiratory distress syndrome
  - Clinical evidence of respiratory distress with radiological evidence (ground glass appearance on CXR)
- Incidence of pneumothorax
  - Incidence of pneumothorax on CXR
- Incidence of pulmonary haemorrhage
  - Clinical evidence of pulmonary haemorrhage
- Mechanical ventilation
- Days of mechanical ventilation
- Use of postnatal corticosteroids for ventilator dependence
- Days of duration of respiratory support (endotracheal ventilation, high-frequency oscillatory ventilation, CPAP, heated humidified high-flow nasal cannula  $O_2$ , low flow nasal cannula  $O_2$ )
- Bronchopulmonary dysplasia (BPD) – supplemental  $O_2$  at 28 days of life
- Chronic lung disease of prematurity (CLD) – need for supplemental  $O_2$  at 36 weeks corrected gestational age (CGA) determined by physiological oxygen reduction test
- Medical treatment for a patent ductus arteriosus
  - Administration of ibuprofen or paracetamol for PDA

- Surgical treatment for a patent ductus arteriosus
- Proven necrotising enterocolitis ( $\geq$  Bell's stage 2)
- Incidence of Intraventricular haemorrhage (IVH) (any and severe: IVH grade  $\geq 3$ )
  - Evidence on surveillance cranial ultrasounds performed regularly in NICU as standard of care
- Incidence of cystic periventricular leukomalacia
  - Evidence on surveillance cranial ultrasounds performed regularly in NICU as standard of care
- Retinopathy of prematurity treated with laser photocoagulation or intravitreal injections
  - Evidence on surveillance ophthalmology review performed regularly in NICU as standard of care
- Death before hospital discharge
- Survival without BPD at hospital discharge
- Survival without CLD at hospital discharge
- Duration of hospitalisation
- Use of home oxygen therapy
  - Discharged home on oxygen therapy

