#### Secondary endpoints analysis

Mortality is an intercurrent event that could potentially occur before observation of many of the secondary endpoints in this trial in addition to the primary endpoint. Most secondary outcomes will involve evaluation of the intervention effect to be expected in infants while alive. Analysis of secondary endpoints will be performed on the intention-to-treat set of all randomised infants. The exceptions to this are

- Number of attempts taken to successfully intubate in the delivery room – will only be assessed for those who need to be intubated in the delivery room (intubation in the delivery room is indicated by variable **dr\_infant\_intub.factor**)
- Rectal temperature on admission to NICU as well as NICU intubation will only be evaluated for infants who are admitted to NICU alive (identified by derived variable **nicu\_admission**)

|         |                                           |              |               |
|---------|-------------------------------------------|--------------|---------------|
| UCD CRC | SAP for the POPART trial                  |              |               |
| UCD CRC | Template: Statistical Analysis Plan (SAP) | Version: 1.0 |               |
|         |                                           |              | Page 13 of 19 |

- Bronchopulmonary dysplasia (BPD) – supplemental O2 at 28 days of life - will only be evaluated for infants who are alive at 28 days of life (infants alive at 28 days to be determined by the variable **bpd\_d28.factor** )
- Chronic lung disease of prematurity (CLD), the need for supplemental O2 at 36 weeks corrected gestational age (CGA) determined by physiological oxygen reduction test - will only be evaluated for infants who are alive at 36 weeks CGA (determined by the variable **cld\_36wks.factor** )
- Duration of hospitalisation will be summarized and analyzed both for infants who survive to hospital discharge and for the whole sample. A similar approach will be used for days of mechanical ventilation and days of respiratory support.

Each categorical secondary endpoint will be analysed using the same approach as the main analysis of the primary endpoint.

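### The NICU intubation endpoint keeps infants already intubated in the delivery room in its denominator as non-events, so other things equal it favours the arm with more delivery-room intubation

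*Combined protocol and SAP*

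**What the plan says.** The protocol (section 10.3) lists "NICU intubation" as a secondary outcome with no definition, and section 11.3.2 has it determined at discharge. The definition appears only in SAP section 1.3: "NICU intubation – first intubation occurring in the NICU". Delivery-room intubation is a separate secondary endpoint in the same list.

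SAP section 5.1.1 sets the default population: "Analysis of secondary endpoints will be performed on the intention-to-treat set of all randomised infants". It then lists exceptions, including: "Rectal temperature on admission to NICU as well as NICU intubation will only be evaluated for infants who are admitted to NICU alive". For another endpoint, the number of delivery-room attempts, the SAP does condition on delivery-room intubation; that endpoint "will only be assessed for those who need to be intubated in the delivery room". It states no such condition for NICU intubation.

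On the method: "Each categorical secondary endpoint will be analysed using the same approach as the main analysis of the primary endpoint". That means a log-binomial relative risk with 95% confidence interval and a two-sided two-proportion Z test. SAP section 2.2 calls p < 0.05 significant for every analysis.

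Both documents expect delivery-room intubation in enrolled infants: "Enrolled infants will be intubated for persistent apnoea and/or bradycardia in the DR, or for respiratory failure in the NICU".

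**The concern.** Delivery-room intubation precludes a first intubation in the NICU. On the natural reading of the two SAP sections, an infant who arrives intubated counts as a non-event for NICU intubation, alongside infants who never needed a tube. Nothing else in the plan deals with this: the estimand table (SAP 1.4.1) and the competing-risks model (SAP 5.1.2) cover only the primary endpoint.

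The comparison therefore depends partly on where infants are intubated as well as on whether they are. A difference between arms in delivery-room intubation is possible in this design. The intervention is given within 5 minutes of birth, caregivers are not masked, and protocol sections 9.2 and 11.3.2 name bradycardia as an effect of surfactant, while persistent bradycardia is a trigger for delivery-room intubation. What is at stake is one superiority test and relative risk whose direction can oppose the effect on intubation overall.

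**Working it through.** **The plan's own figure.** Protocol 14.2 assumes 46% v 28%, 80% power and two-sided 5%. With the pooled two-proportion formula and mean rate 0.37:

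n per arm = [1.960 × √(2 × 0.37 × 0.63) + 0.842 × √(0.46 × 0.54 + 0.28 × 0.72)]² / 0.18² = 111.8, rounded up to 112.

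The total is 224, as stated, and 224/0.9 = 249, against the plan's 250. The sample size reproduces and is not touched by this point. The documents give no figure for NICU intubation.

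**Inputs for the check.**
- 125 infants per arm: 250/2, assuming all are admitted alive.
- d0, d1: share intubated in the delivery room in the first and second arm. The documents give neither, so all values are assumptions.
- q: risk of a first NICU intubation among infants not intubated in the delivery room. Also an assumption.
- 46%: the protocol's control rate, used in case B. It is a 120-hour rate, whereas NICU intubation runs to discharge, so it serves only as an illustration.

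**Case A: q equal in both arms.** The endpoint rate is (1 − d) × q, so q cancels and RR = (1 − d1)/(1 − d0). Intubation in either place is d + (1 − d) × q. With q = 46%:

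| Delivery room, d0 v d1 | NICU intubation as defined | RR | Intubation in either place | RR |
|---|---|---|---|---|
| 10% v 15% | 41.4% v 39.1% | 0.944 | 51.4% v 54.1% | 1.053 |
| 10% v 20% | 41.4% v 36.8% | 0.889 | 51.4% v 56.8% | 1.105 |
| 10% v 30% | 41.4% v 32.2% | 0.778 | 51.4% v 62.2% | 1.210 |

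The fourth column uses q = 46%; the NICU RR holds for any q. In each row the endpoint points towards the second arm while that arm has more intubation in total. The chance of p < 0.05 on NICU intubation is about 6%, 11% and 33% respectively.

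**Case B: total intubation fixed at 46% in both arms.** The endpoint rate is 0.46 − d. With d = 10% v 20% it is 36% v 26%, RR 0.72, with about a 40% chance of p < 0.05, although the RR for intubation in either place is 1.00.

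**The two cases compared at 15% v 30%.**
- Case B: 0.46 − 0.15 = 31% v 0.46 − 0.30 = 16%. z = 2.80, p = 0.005; about 80% chance of p < 0.05.
- Case A with the same first-arm rate: q = 0.31/0.85 = 36.5%, so 31% v 0.70 × 36.5% = 25.5%. z = 0.96, p = 0.34; about 16% chance of p < 0.05. Intubation in either place is 46% v 30% + 25.5% = 55.5%.

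**Would restricting the denominator help?** Among infants not intubated in the delivery room, case A gives RR 1.00. Case B at 10% v 20% gives 0.36/0.90 = 40.0% v 0.26/0.80 = 32.5%, RR 0.81. The restriction conditions on a post-randomisation event and does not remove the artefact in general. Counting intubation in either place does so in both cases.

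**The case against.** A reader might infer that delivery-room-intubated infants are counted as never intubated, or that the plan would report a false benefit unopposed. The documents do not support either. These infants are events for delivery-room intubation, which is tested in the same way. At 15% v 30% that test gives z = 2.84 and p = 0.0045 against the second arm, slightly stronger than the NICU artefact in case B. The primary analysis would show no benefit in either case. It already comes close to inference on intubation in either place, because delivery-room intubation is described under the primary endpoint and intubations short of the strict criteria are counted.

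A large artefact also needs strong assumptions. The figure of about 80% requires every extra delivery-room intubation to replace one that would have occurred in the NICU. The adverse-reaction table in protocol 13.3 lists bradycardia and decreased oxygen saturation as rare, so a doubling of delivery-room intubation has no support in the documents. The direction, too, holds only with other things equal: if the extra infants intubated in the delivery room would never have been intubated in the NICU, the NICU rate does not fall.

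Finally, the coding of `first_intubation_nicu.factor` is not printed. Non-event is the natural reading, but a missing code cannot be excluded. That would not settle matters: the analysis would condition on a post-randomisation event, and with 5% to 40% missing, SAP 5.3 calls for multiple imputation of the values.

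All of this limits the size. It leaves standing that the SAP gives this endpoint its own test and relative risk, states no rule for these infants, and does not require the two intubation rows to be read together.

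**Conclusion.** The point holds as a minor issue. As the SAP reads, and with other things equal, the relative risk and Z test for NICU intubation favour the arm with more delivery-room intubation. Under equal NICU risk the distortion is exactly (1 − d1)/(1 − d0): 0.89 for 10% v 20% and 0.78 for 10% v 30%. How often it would reach significance cannot be fixed from the documents; at 15% v 30% it ranges from about 16% to about 80% between the two cases. The delivery-room rates, the NICU risk and 125 admitted alive per arm are assumptions, and non-event coding is inferred. The documents do not support a claim that surfactant will raise delivery-room intubation, or that the primary endpoint or sample size is affected. No stopping rule rests on this endpoint.

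**What to change.** In the SAP:

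1. State how `first_intubation_nicu.factor` is coded for infants intubated in the delivery room.
2. Present first intubation as one table in all randomised infants, by arm: delivery room, NICU, never.
3. Draw comparative inference on intubation in either place, and state its time window.
4. Label the NICU row descriptive, to be read only with the delivery-room row.
5. Record this in SAP section 6 as a change from protocol 14.5.2, which calls for a superiority test of each categorical secondary endpoint. Record there too that the restriction to first intubation was added in the SAP.

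The cost is one stand-alone p-value and a documented departure from the protocol. Both variables are already named in the SAP, so no new data are needed.

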## 1.4 Estimands

### 1.4.1 Primary estimand

The primary estimand in this trial is the difference in the rates of endotracheal intubation for respiratory failure while alive within 120 hours of birth in future infants treated with prophylactic oropharyngeal surfactant compared to infants treated with the standard of care (no intervention). Two potential intercurrent events were identified that could impact on observation of the primary endpoint: (1) death prior to 120 hours without observation of the primary endpoint and (2) intubation for respiratory failure without meeting the pre-specified criteria defined in the protocol.

| Intercurrent event                                                                     | Strategy for handling intercurrent event                                                                                                                                                                                       |
|----------------------------------------------------------------------------------------|--------------------------------------------------------------------------------------------------------------------------------------------------------------------------------------------------------------------------------|
| (1) Infants who died within 120 hours of birth without having met the primary endpoint | While alive strategy – data collected on the subjects while alive will be used to determine the primary endpoint, even if the observation period is shorter than 120 hours                                                     |
| (2) Infants intubated for respiratory failure within 120 hours of birth without        | Treatment policy strategy – subjects will be considered to have met the primary endpoint if they are intubated for respiratory failure within 120 hours of life (regardless of whether or not the protocol definition was met. |

|         |                          |  |
|---------|--------------------------|--|
| UCD CRC | SAP for the POPART trial |  |
|---------|--------------------------|--|

|         |                                           |              |              |
|---------|-------------------------------------------|--------------|--------------|
| UCD CRC | Template: Statistical Analysis Plan (SAP) | Version: 1.0 |              |
|         |                                           |              | Page 7 of 19 |

|                                                |  |
|------------------------------------------------|--|
| meeting the criteria specified in the protocol |  |
|------------------------------------------------|--|

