| Statistical methods                           | 
Comparison of the primary outcome (intubation for respiratory failure within 120 hours of birth) and each dichotomous secondary outcome between oropharyngeal surfactant at birth and no intervention, using a two-sided two proportion Z test.
 
Comparison of continuous secondary outcomes between oropharyngeal surfactant at birth and no intervention, using independent samples t-tests.
 
Regression analysis will be carried out to determine the sensitivity of the treatment effect to relevant covariates (such as gestational age)
 |
| Sample size                                   | A sample size of 250 is required to detect a difference of 18% in the rate of intubation between infants receiving oropharyngeal surfactant at birth and no intervention with a statistical power of 80%, at a significance level of 5%. This calculation assumes an anticipated loss-to-follow-up of 10% of recruited infants.                                                                                                                                                                                                                                  |

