#### 11.3.6 Method of assigning Subjects to treatment groups

Infants will be randomised to receive oropharyngeal surfactant or CPAP (which is the standard of care) in a 1:1 ratio using variable block randomisation, with block sizes of 4, 6 and 8. Randomisation will be stratified by participating centre. The more prematurely an infant is born, the higher their risk is of being

intubated for respiratory support in the first 120 hours of life (primary outcome). It is important to ensure balance in the risk of reaching the primary outcome between the two treatment arms at study entry; thus we will also stratify the randomisation by gestational age (<26 weeks and 26-28 weeks inclusive).

Infants of multiple gestations will be randomised as individuals.

A computer-generated randomisation schedule will be prepared by an independent statistician who will not be involved with subsequent data analysis or interpretation. The schedule will be stored securely on a password protected computer. The randomization list will be numbered using sequential 6-digit randomization codes (e.g. NMH001, NMH001,...). Each group assignment – “OROPHARYNGEAL SURFACTANT” or “CONTROL” – will be written on a card that will be labelled with its corresponding 6-digit randomisation code (e.g. NMH001). Each card will be folded in half and placed in an opaque sealed envelope that will be labelled with the same 6-digit randomisation code. The envelopes will then be placed in sequential order (e.g. NMH001, NMH002, NMH003...) in separate boxes for the two gestational age strata for each centre. At each centre, the boxes containing the envelopes will be stored securely in the neonatal intensive care unit (NICU), as the clinical team will need to have access to the randomisation envelopes. An envelope from the appropriate box (<26 weeks or 26–28 weeks) will be opened immediately before birth.

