### 14.2 Determination of sample size subjects

In randomised studies, the rate of mechanical ventilation in the days after birth among preterm infants treated with CPAP alone has varied from 46– 60%. (2, 11, 19-21) Minimally invasive surfactant techniques were shown to reduce the rate of mechanical ventilation to from 46% to 28% in a cohort of infants with a gestational age between 26 and 28 weeks. (21)

Sample size for this study was calculated in G\*power, using a two-sided, two-proportion Z test. To detect a difference in the rate of endotracheal intubation for respiratory failure of 18% between treatment arms (assuming a rate of 46% in the control group and 28% in the intervention arm) with 80% power and a 5% significance level, a sample size of 224 infants would be required. To compensate for a death rate of 10% (estimated from local data, The National Maternity Hospital, Neonatal Clinical Report for 2015) before the primary outcome can be determined (i.e. at 120 hours), we will need to recruit a total of **250** infants to this study.

The National Maternity Hospital is a stand-alone university maternity hospital with a tertiary NICU to which > 150 infants < 1500g are admitted annually. We have a track record of initiating, conducting, completing, presenting and publishing investigator-led randomised controlled trials, including trials that compared delivery room interventions, (12-14) trials that had respiratory failure in the NICU as the primary outcome (15) and trials that compared investigational medicinal products (16) in preterm infants. Though the enrolment rates to our studies amongst eligible infants are consistently excellent (> 80%), we believe it will be necessary to enrol infants at multiple sites in order to enrol our planned target sample of 250 infants in a timely fashion. We have a track record enlisting the help of collaborators

nationally(16)andinternationally(14, 17)to perform our studies. We believe that with their help, we can enrol these infants in 2–3 years.

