## 5. Analysis

### 5.1 Analysis methods

#### 5.1.1 Primary analysis

The primary estimand in this trial is the difference in the rates of endotracheal intubation for respiratory failure while alive within 120 hours of birth in future infants treated with prophylactic oropharyngeal surfactant compared to infants treated with the standard of care (no intervention). The primary analysis will be done on the full analysis set according to the intention-to-treat principle. For infants who died within 120 hours of randomization, the primary endpoint will be documented for the time period in which they were alive. Infants who were intubated without (or prior to) meeting the definition of respiratory failure defined in the protocol will be included, and will be considered to have met the primary endpoint in the main analysis.

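### An infant who dies before 120 hours without intubation counts as not meeting the primary endpoint, no analysis of that endpoint counts the death as unfavourable, and the sample size assumes such infants have no outcome

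*Combined protocol and SAP*

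**What the plan says.** SAP 1.4.1 names death before 120 hours without the primary endpoint as an intercurrent event and assigns it a while-alive strategy: "data collected on the subjects while alive will be used to determine the primary endpoint", even when observation is shorter than 120 hours. SAP 5.1.1 repeats the rule: "For infants who died within 120 hours of randomization, the primary endpoint will be documented for the time period in which they were alive". The full analysis set (SAP 3.2.1) is all randomised infants. The primary test (SAP 5.1.1) is an unadjusted two-sided two-proportion Z test on numbers meeting and not meeting the endpoint.

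SAP 5.1.2 lists four sensitivity analyses for the primary endpoint: covariate-adjusted GEE, a competing-risks model that names early death, recoding of off-criteria intubations as negative, and per protocol.

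The sample size starts from a different premise. Protocol 14.2 finds that "with 80% power and a 5% significance level, a sample size of 224 infants would be required", "assuming a rate of 46% in the control group and 28% in the intervention arm". It then raises the number to 250, with the words "To compensate for a death rate of 10" per cent, because those infants die before the outcome can be determined. The protocol synopsis labels the same allowance differently: "This calculation assumes an anticipated loss-to-follow-up of 10% of recruited infants". SAP section 6 reports no departure from the protocol's main statistical features.

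**The concern.** Death without intubation is a bad outcome that the primary endpoint records as the better of its two categories. The SAP does not say this in words, but it follows from the while-alive rule applied to all randomised infants. In an open-label trial of infants born before 29 weeks, an arm with more early un-intubated deaths would look better on the headline result, and no planned analysis of that endpoint would show it.

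The sample-size premise is a second problem. The protocol removes early deaths from the calculation, the SAP keeps them in the test, and the synopsis describes them as lost to follow-up. The power statement therefore refers to a data set that the SAP will not analyse.

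**Working it through.** **Inputs.** From protocol 14.2: 46% control, 28% intervention, two-sided Z test, 5% level, 80% power, 224 infants, 10% deaths. Allocation is 1:1 (protocol 11.3.6), so 250 gives 125 per arm. Assumed, because the documents do not give it: d, the share of infants who die before 120 hours without intubation.

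**1. Reproducing the plan's figure.** With pooled variance under the null,

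n per arm = [1.96·√(2p̄(1−p̄)) + 0.8416·√(p₁(1−p₁)+p₂(1−p₂))]² / (p₁−p₂)².

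For p₁ = 0.46, p₂ = 0.28 and p̄ = 0.37, the roots are 0.6828 and 0.6708. So n = (1.3382 + 0.5646)² / 0.0324 = 111.75, rounded up to 112 per arm, or 224. Then 224/0.9 = 248.9, or 250 in equal arms. Both figures reproduce. The second does so only if 10% of infants supply no primary outcome: 112.5 per arm, power 80.3%.

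**2. Power as the SAP will analyse.** Power = Φ{[(p₁−p₂)√125 − 1.96·√(2p̄(1−p̄))] / √(p₁(1−p₁)+p₂(1−p₂))}.

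- If 46% and 28% already describe all randomised infants: (2.0125 − 1.3382)/0.6708 = 1.005, power 84.3%.
- If they describe the other infants, both rates are multiplied by (1−d), with d equal in the two arms:

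| d | Control | Surfactant | Power at 125 per arm | Total for 80% |
|---|---|---|---|---|
| 0% | 46.0% | 28.0% | 84.3% | 224 |
| 2% | 45.1% | 27.4% | 83.1% | 232 |
| 5% | 43.7% | 26.6% | 81.2% | 244 |
| 10% | 41.4% | 25.2% | 77.9% | 264 |

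Power crosses 80% at d of about 6.9%.

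**3. Direction when deaths differ by arm.** Assume no effect on intubation (46% among the other infants in both arms) and un-intubated deaths of 5% control and 10% surfactant.

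- Primary as planned: 0.46 × 0.95 = 43.7% against 0.46 × 0.90 = 41.4%, which favours surfactant by 2.3 points (relative risk 0.95).
- Intubation or death: 0.05 + 0.437 = 48.7% against 0.10 + 0.414 = 51.4%, which favours control by 2.7 points.

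The sign reverses. For scale, the standard error of the primary difference at 125 per arm is √(0.4255 × 0.5745 × 2/125) = 6.3 points.

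**4. Whether a planned analysis covers this.** The adjusted GEE and the recoding of off-criteria intubations keep the same rule for deaths. The competing-risks model treats death as a competing event, not a failure, and its type is not stated. A cumulative-incidence version would move in the same direction as the primary. A cause-specific version would censor the deaths. The per-protocol set drops incomplete primary data without saying whether early deaths qualify. The best-case and worst-case analysis in SAP 5.3 is for missing data, and under the while-alive rule these infants are not missing. SAP 5.4 counts deaths per arm, but not by 120 hours or by intubation status.

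**The case against.** The handling of death is open and pre-specified. While-alive is a recognised strategy, and a composite would ask a different question. That stands, and it is why the primary estimand should not change.

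A reader might infer that nothing in the plan counts death as a failure. The documents do not support that. Death before discharge has Kaplan-Meier and Cox analyses (SAP 5.1.1) and an interim boundary of p < 0.001 (SAP 2.3). Survival without BPD and survival without CLD are secondary endpoints (SAP 1.3). These are separate endpoints assessed to discharge, so they do not qualify the 120-hour intubation result. The gap concerns the primary endpoint only.

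A reader might also infer that the trial falls short of 80% power. That needs two conditions that protocol 14.2 does not state: that 46% and 28% exclude infants who die un-intubated, and that about 7% or more of infants die that way. The plan's 10% is all deaths before 120 hours. Infants intubated for respiratory failure before dying have already met the endpoint, so 10% is an upper bound under the plan's own figure.

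Finally, the illustrated shift of 2.3 points is under half a standard error. It would seldom produce a significant result alone, and a large imbalance in deaths would show in the planned mortality reporting. That limits the size of the problem. It does not remove the direction of the bias.

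**Conclusion.** The point holds for the primary endpoint and should be fixed. Early un-intubated deaths count as non-events, no analysis of that endpoint counts them as unfavourable, and any imbalance moves the result towards the arm with more such deaths. The size depends on a share that the documents do not give. If almost no infant dies un-intubated, the effect is negligible. At the assumed 5% and 10%, the apparent benefit is 2.3 points and the composite points the other way.

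The sample-size arithmetic is correct, but its premise contradicts the SAP, and the synopsis adds a third description. Power at 250 lies between 77.9% and 84.3%. This range straddles the 80% target, so it is a wording and consistency error and not an established loss of power.

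A reader might go further and require the composite to agree in direction before benefit is claimed. That would be an added success rule and a matter of choice; nothing in the documents calls for it.

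**What to change.** Keep the primary estimand.

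- In SAP 5.1.2, add a supportive analysis of intubation for respiratory failure or death within 120 hours, by the same unstratified method as the primary (two-proportion Z test, and relative risk from log-binomial regression on treatment). Specify it before results by arm are seen.
- Tabulate, by arm, infants who died before 120 hours without intubation.
- Reconcile protocol 14.2, the synopsis and SAP 1.4.1. State that early deaths stay in the denominator as non-events. Say whether 46% and 28% refer to all randomised infants or to the others. Give power as about 78% to 84% for 10% down to 0% un-intubated deaths.

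The cost is one extra analysis and one table, on data already collected, and a stated power slightly less favourable at the lower end. The endpoint and the sample size do not change. The supportive analysis should not be presented as powered: with 46% and 28% among the other infants, its power at 250 is 79.1% with 5% un-intubated deaths (48.7% against 31.6%) and 73.7% with 10% (51.4% against 35.2%).
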